### Patient selection

40 patients should be enrolled in this clinical study fulfilling the following inclusion criteria.

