### Sample Size Calculation

The sample size calculation is based on the analysis of the primary endpoint PFS-3yR, denoting the rate of progression-free survival after 3 years of follow-up. The trial is designed to detect an improvement by 20% in this primary endpoint. For sample size calculation, the following hypotheses will be made:

• p_0 _is the largest PFS-3yR which, if true, implies that the efficacy of the treatment is too low. In the present trial p_0 _has been taken as 50%.

• p_1 _is the lowest PFS-3yR which, if true, implies that the efficacy of the treatment is adequate. In the present trial p_1 _has been taken as 70%.

• α is the accepted probability of considering adequate efficacy of the treatment with a true PFS-3yR equal or lower to p_0_. In the present trial α has been taken as 5% (actual 0.049).

• β is the accepted probability of rejecting adequate efficacy of the treatment with a true PFS-3yR at least equal to p_1_. In the present trial α has been taken as 20% (actual 0.0193).

Using the one-sided binomial test with the given hypotheses, the study required 37 patients to decide whether the PFS-3yR is less than or equal to 0.5 or greater than or equal to 0.7. If the number of progressions or deaths is lower than 13, the hypothesis that PFS-3yR ≤ 0.5 is rejected with a target error rate of 0.05 and an actual error rate of 0.049. Sample size calculation was done using the software PASS 2008.

Allowing for approximately 10% non-evaluable patients primarily due to drop out, n = 40 patients will be recruited.

Assuming the distribution of PFS events is exponential, PFS-3yR = 0.5 resp. PFS-3yR = 0.7 is equivalent to a median PFS = 3 years resp. median PFS = 5.8 years.

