### Statistical Methods

#### Confirmatory Analysis

The primary aim and its corresponding endpoint are subject to a confirmatory statistical analysis. The primary aim is to evaluate efficacy of carbon ion boost in combination with postoperative photon radiotherapy in patients with atypical meningiomas Simpson grade 4 and 5 on progression-free survival rate after 3 years of follow-up (PFS-3yR). Formally,

H_0_: PFS-3yR ≤ 0.5 versus H_1_: PFS-3yR > 0.5.

PFS-3yR is statistically tested with a one-sided binominal test on the level α = 5%.

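### Forty patients cover a 7.5% loss, not the stated approximate 10%; a 10% loss leaves 36 evaluable and, if drop-outs are left out of the test, about 74% power

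*Protocol article*

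**What the plan says.** In Sample Size Calculation the null three-year progression-free rate is 50%, the alternative is 70%, the one-sided level is 5% with an actual value of 0.049, and the type II error is 20%. From these inputs, "the study required 37 patients to decide whether" the rate is at most 0.5 or at least 0.7. The rule printed there rejects the null when there are fewer than 13 progressions or deaths. The allowance follows: "Allowing for approximately 10% non-evaluable patients primarily due to drop out, n = 40 patients will be recruited".

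Patient selection repeats the target: "40 patients should be enrolled in this clinical study". Confirmatory Analysis names the exact one-sided binomial test at 5% as the only confirmatory test.

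Full Analysis Population keeps patients who withdraw or go off study once treatment has begun. It removes only those who withdraw consent before treatment and those found to have violated major eligibility criteria. The article does not say how a patient without a known three-year status enters the binomial test.

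**The concern.** The recruitment figure does not follow from the two figures beside it. If 37 evaluable patients are needed and about 10% are expected to be lost, 40 is too few under either common way of inflating.

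The reader is led to believe that the 20% type II error survives the planned loss. This is the only confirmatory test in a single-arm trial of 40 patients. Its cut-off is given for one sample size only, although the number of evaluable patients will not be known until follow-up ends.

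**Working it through.** **Inputs**, all from Sample Size Calculation and Confirmatory Analysis: p0 = 0.50, p1 = 0.70, one-sided level 0.05, 37 evaluable, 40 recruited, loss of about 10%.

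**Method.** Let S be the number of patients progression-free at three years among n evaluable, with P(S ≥ r | n, p) = Σ C(n,k) p^k (1−p)^(n−k), summed over k = r to n. The critical r is the smallest with P(S ≥ r | n, 0.5) ≤ 0.05. Power is P(S ≥ r | n, 0.7). The largest event count that still rejects is n − r.

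**Step 1: reproduce the plan.** For n = 37, r = 24, so 13 or fewer events reject. Alpha = 0.0494 and power = 0.8071, so the type II error is 0.193. This matches the stated 37 patients, the alpha of 0.049 and the 20% target. No n from 30 to 36 reaches 80% power.

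**Step 2: the allowance.**
- Losses covered: 40 − 37 = 3, and 3/40 = 7.5%.
- Evaluable after a 10% loss: 40 × 0.90 = 36.
- Inflation by division: 37/0.90 = 41.1, so 42. By multiplication: 37 × 1.10 = 40.7, so 41. Neither gives 40.

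**Step 3: power by evaluable number**, each at its own 5% cut-off.

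| Evaluable n | Rejects at most (events) | Alpha | Power |
|---|---|---|---|
| 35 | 12 | 0.0448 | 77.3% |
| 36 | 12 | 0.0326 | 73.7% |
| 37 | 13 | 0.0494 | 80.7% |
| 38 | 13 | 0.0365 | 77.5% |
| 39 | 13 | 0.0266 | 74.0% |
| 40 | 14 | 0.0403 | 80.7% |

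At 36 the type II error is 1 − 0.737 = 0.263, against the planned 0.20.

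**Step 4: random loss.** Assume each of the 40 patients is lost independently with probability 10%. The chance of keeping at least 37 is then 42%, and power averaged over the evaluable number is about 75.5%. A loss of about 10% thus gives power of roughly 74 to 76%.

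**Step 5: one cut-off for all n.** The cut-off of 13, which matches the stated alpha at 37, would give 36 patients an alpha of 0.0326 + C(36,13)/2^36 = 0.0326 + 0.0336 = 0.066, above 5%. The printed cut-off of 12, carried to 40 patients, would give alpha 0.0083 and power 57.7%. A cut-off worked out for one n is not safe at another.

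**The case against.** Four points can be made for the plan.

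- **The allowance is only approximate.** This stands. The shortfall is one or two patients, so this is loose rounding and not a gross sample size error.

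- **The 74% is partly a property of the exact test.** This also stands. One loss (39 evaluable) gives 74.0%, and five losses (35 evaluable) give 77.3%, more than four do. A reader might infer that recruiting 42 would restore 80% power. It would not do so reliably, because 42 with 4 losses leaves 38 and power of 77.5%.

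- **Drop-outs may not leave the test.** Full Analysis Population retains those who leave after treatment has begun, and a fuller analysis plan may state how they count. The 73.7% therefore depends on the sample size section's own premise that drop-outs are non-evaluable. That premise is the plan's, so the calculation is fair on its terms, but the two sections do not agree.

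- **The printed rule remains valid at 36.** A reader might infer that losing one patient invalidates the printed critical value. It does not: fewer than 13 events means at most 12, which is the correct 5% rule for 36. At 37 that printed rule gives alpha 0.0235 and power 69.8%, so under it power is higher at 36 than at 37. The mismatch between the printed cut-off and the stated alpha is a separate fault. The comparison here uses 13 or fewer events at 37 because only that cut-off gives the stated 0.049 and about 80% power.

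**Conclusion.** The point holds in a limited form. Forty recruited patients cover 3 losses (7.5%), not about 10%. At a 10% loss 36 remain and power is 73.7% instead of 80.7%, so the type II error is about 26% and not the stated 20%. With losses random at 10%, average power is about 75.5%.

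This rests on three assumptions: drop-outs are left out of the binomial test, loss is unrelated to outcome, and the cut-off is reset to the 5% value for the number actually evaluable.

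The documents do not support calling the trial seriously undersized, nor attributing the whole fall in power to the missing patient. The fault is a stated allowance and power that do not fit together, with a single cut-off for an evaluable number that is bound to be uncertain.

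**What to change.** Change the text of Sample Size Calculation, with no added patients:

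1. State that 40 patients allow for 7.5% (3 of 40) non-evaluable, and that a loss of about 10% gives power of about 74 to 76%.
2. Replace the single cut-off by the 5% critical value for each evaluable number: at most 12 events for 35 or 36 patients, at most 13 for 37 to 39, and at most 14 for 40.
3. Say whether a patient who drops out after treatment has begun leaves the binomial test or stays in it, and if so how that patient counts, so that this section and Full Analysis Population agree.

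The cost is a few sentences and a slightly less favourable stated allowance or power. Replacing the primary test is a separate matter and is not needed for this correction.

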### Analysis Variables

The primary outcome variable is progression-free survival rate at 3 years. Secondary objectives are the assessment of overall survival as well as 'toxicity' and 'safety'.

### Analysis Populations

#### Full Analysis Population

The full analysis set (FAS) according to intention to treat (ITT) consists of all patients included in the trial irrespective whether any protocol violation was present at the time of treatment start or during treatment under study conditions or whether the patient withdrew consent or was taken off-study any time after treatment start.

Not included are patients who withdraw informed consent before start of treatment or about whom it becomes known that major in/exclusion criteria were violated which would have excluded them from study treatment when known at start of treatment.

#### Per Protocol Population

The per protocol population comprises only patients meeting eligibility criteria and receiving treatment according to this protocol.

#### Safety Population

All patients of the FAS receiving the study treatment at least once are part of the safety population.

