## Methods and Design

The purpose of the trial is to evaluate a carbon ion boost to the macroscopic tumor in combination with photon radiotherapy in patients atypical meningiomas.

The aim of the study is to compare progression-free survival as a primary endpoint, and overall survival free survival, toxicity and safety as secondary endpoints.

The primary objective is progression-free survival rate during the follow-up phase of at least 3 years. The secondary objectives of the study are overall survival, toxicity and safety.

The trial will be performed as a single-center one-armed Phase II study.

Patients fulfilling the inclusion criteria will be included.

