#### Descriptive Analysis

Secondary endpoints are all of explorative nature and reported using descriptive analysis methods.

• For failure time data (progression-free survival and overall survival) Kaplan-Meier curves will be displayed and median estimates as well as associated 95% confidence intervals will be reported.

• Safety/tolerability will be assessed by the type, incidence, severity (graded by the NCT CTCAE Version 4.0), and relatedness of AEs to treatment and by assessment of all parameters related to safety. Tolerability and dosing will be described by numbers of patients in whom treatment was given as planned, delayed or permanently stopped.

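### The safety population is drawn from a full analysis set that removes patients later found to violate major eligibility criteria, so some treated patients are left out of the toxicity analysis

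*Protocol article*

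**What the plan says.** Three parts of the protocol article bear on this.

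- **Full Analysis Population.** The first sentence describes an intention-to-treat set of all included patients, "irrespective whether any protocol violation was present at the time of treatment start or during treatment under study conditions". The next sentence takes out two groups: patients who withdraw consent before treatment starts, and patients "about whom it becomes known that major in/exclusion criteria were violated which would have excluded them from study treatment when known at start of treatment".
- **Safety Population.** "All patients of the FAS receiving the study treatment at least once are part of the safety population".
- **Descriptive Analysis.** "Safety/tolerability will be assessed by the type, incidence, severity", together with relatedness to treatment. No analysis set wider than the safety population is named here.

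Safety is a declared aim of the trial. Under Methods and Design: "The secondary objectives of the study are overall survival, toxicity and safety". A separate per protocol population already exists for patients who are eligible and treated as planned.

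**The concern.** A safety set normally contains everyone exposed to the treatment, because toxicity follows exposure and not eligibility. Here membership depends first on surviving the FAS exclusion, and that exclusion is written for violations that were not known when treatment began. It can therefore reach patients who have already been irradiated.

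The stake is the toxicity estimate, a stated secondary objective of a small single-arm trial. Some exclusion criteria, such as previous radiotherapy of the brain, plausibly mark patients at higher risk of toxicity. If such patients are the ones removed, the reported rate would be too low.

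The FAS definition also pulls in two directions. Its first sentence keeps patients whatever violation was present at treatment start; its second removes some patients for exactly such a violation. Since the FAS is labelled intention to treat, the ambiguity carries over to the denominator of the primary test.

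**Working it through.** **1. Who is in which set.** Take a patient who received the boost and was later found to have violated a major criterion.

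| Set | Rule | Is this patient in it? |
|---|---|---|
| FAS | all included, minus later-discovered major violators | no |
| Safety | FAS and treated at least once | no, because not in the FAS |
| Per protocol | eligible and treated per protocol | no |

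The patient belongs to none of the three defined sets. Patients who withdraw consent before treatment raise no safety issue, because they were not exposed. The gap is confined to treated patients with a late-discovered major violation.

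**2. Possible effect on toxicity.** Input from Sample Size Calculation: "n = 40 patients will be recruited". Let k be the number of treated patients removed. The documents do not give k; I assume 0 to 4.

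- Weight of one patient: 1/40 = 2.5%.
- If no event is seen, the one-sided 95% upper limit is 1 − 0.05^(1/n). For n = 40 it is 7.2%; for n = 36 it is 8.0%. The loss of precision is small.
- The possible bias is larger. Assume 4 severe events among 40 treated patients, a true observed rate of 4/40 = 10%:
  - two removed, both with an event: 2/38 = 5.3%;
  - four removed, all with an event: 0/36 = 0%;
  - four removed, none with an event: 4/36 = 11.1%.

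The event counts are assumptions chosen to show the range. They are not forecasts.

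**3. The plan's own design figure.** The article gives 37 evaluable patients for a one-sided exact binomial test of 0.5 against 0.7, with an actual error rate of 0.049. With 24 or more progression-free patients out of 37 (13 events or fewer), P(X ≥ 24 | 37, 0.5) = 0.0494 and power at 0.7 is 0.807. The smallest n meeting both targets is 37, so the figure reproduces. The event limit printed in the text is lower than 13, which does not match 0.049. That is a separate matter; below I apply the 5% level fixed under Confirmatory Analysis.

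**4. Sensitivity of the primary decision to one removal.** The largest event count that still rejects at 5% is:

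| n | 36 | 37 | 38 | 39 | 40 |
|---|---|---|---|---|---|
| events | 12 | 13 | 13 | 13 | 14 |

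Exact p-value = P(X ≥ n − events | n, 0.5).

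Removing one patient **with** an event, starting one event above the limit:

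| Before | p | After | p | Decision changes? |
|---|---|---|---|---|
| 15/40 | 0.077 | 14/39 | 0.054 | no |
| 14/39 | 0.054 | 13/38 | 0.036 | yes |
| 14/38 | 0.072 | 13/37 | 0.049 | yes |
| 14/37 | 0.094 | 13/36 | 0.066 | no |

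Removing one patient **without** an event can work the other way: 14/40 (p = 0.040, rejects) becomes 14/39 (p = 0.054, does not), and 13/37 (p = 0.049) becomes 13/36 (p = 0.066).

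**The case against.** The best defence is that the exclusion is a narrow exception to a general rule. Only violations of major criteria that would have barred treatment trigger it. Minor ineligibility, violations during treatment and withdrawal after treatment start all leave the patient in the FAS. The number affected may be zero. Safety is analysed descriptively, and no test or stopping rule depends on its denominator. All of this stands and limits the size of the problem. It does not answer the point about the safety set: no reason is given for tying exposure-based reporting to eligibility, and no rule returns such patients to the toxicity tables.

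A reader might go further than the text allows in four ways.

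- *That toxicity will be understated.* This is plausible if violators are at higher risk, but the arithmetic shows the rate can also rise. The documents do not settle the direction.
- *That exclusions will be made with outcomes in view.* Nothing says so. The list of major criteria, the timing of the review and who decides may properly stand in an analysis plan or full protocol that is not shown; their absence from an article is not a fault.
- *That adverse events go unrecorded for these patients.* The text removes them from an analysis set. It does not stop recording under CTCAE.
- *That any single removal can turn failure into success.* Among sizes 36 to 40 this happens only at exactly 14 events, going from 39 to 38 or from 38 to 37. It does not happen from the planned 40 or the required 37.

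**Conclusion.** The point holds for the definitions as written. A treated patient later found to have violated a major criterion is outside the safety population, so reported toxicity would not be the rate among all treated patients. This is a stated rule that needs correcting, not a detail left for later. An analysis plan that followed it would carry the problem forward.

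The size cannot be fixed from the documents. It is nil if no such patient occurs, and 2.5% of the set for each one that does. The illustrated range rests on an assumed four removals and four events.

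For efficacy the consequence is secondary but real. The two FAS sentences need reconciling because a change of one patient can alter the confirmatory decision in either direction at certain event counts. The sample size of 37 evaluable and 40 recruited is unaffected.

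**What to change.** 1. **Safety population:** define it as all patients who received at least one fraction of study treatment, regardless of eligibility and of FAS membership.
2. **FAS:** reconcile the sentence that keeps patients despite any violation with the sentence that removes some of them. Limit the exclusion to eligibility criteria fixed before treatment, and have it judged without knowledge of progression, death or toxicity. Dropping the exclusion altogether and leaving eligibility to the per protocol set is a possible alternative, but it is a trade-off for the trial team and is not needed to correct the safety set.

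Cost: two reworded definitions and perhaps a few more patients in the toxicity tables. No new data, visits or patients are needed.

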### Exclusion criteria

Patients presenting with any of the following criteria will not be included in the trial:

- refusal of the patients to take part in the study

- previous radiotherapy of the brain

- time interval of >12 weeks after primary diagnosis (neurosurgical intervention) and beginning of study treatment

- optic nerve sheath meningioma (ONSM)

- Patients who have not yet recovered from acute toxicities of prior therapies

- Known carcinoma <5 years ago (excluding Carcinoma in situ of the cervix, basal cell carcinoma, squamous cell carcinoma of the skin) requiring immediate treatment interfering with study therapy

- Pregnant or lactating women

- Participation in another clinical study or observation period of competing trials, respectively.

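### The safety population is nested in the FAS, so treated patients later found to breach a major entry criterion drop out of the summarised toxicity rates

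*Protocol article*

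**What the plan says.** Toxicity and safety are secondary endpoints of this single-arm trial of 40 patients (Protocol article, Methods and Design; Patient selection; Analysis Variables).

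- **Safety Population:** "All patients of the FAS receiving the study treatment at least once are part of the safety population". No other safety set is defined.
- **Full Analysis Population, first paragraph:** patients stay in the set "irrespective whether any protocol violation was present at the time of treatment start", and also if they withdraw or are taken off study after treatment has begun.
- **Full Analysis Population, second paragraph:** two groups are left out. One is patients who withdraw consent before treatment starts. The other is patients of whom it emerges that "major in/exclusion criteria were violated which would have excluded them from study treatment when known at start of treatment".
- **Exclusion criteria:** the list includes "Patients who have not yet recovered from acute toxicities of prior therapies", "Pregnant or lactating women" and "previous radiotherapy of the brain".
- **Descriptive Analysis:** "Safety/tolerability will be assessed by the type, incidence, severity" and relatedness of adverse events. This section does not name the population on which the tables are built.

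**The concern.** A safety set answers what happened to the people who were exposed. Membership should therefore depend on exposure, not on whether the patient should have been enrolled. Here it depends on both, because the set inherits the FAS exclusion for eligibility.

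That exclusion is not plainly neutral for toxicity. Some entry criteria, such as recovery from acute toxicity of earlier treatment, plausibly relate to the risk of harm. If a treated patient is removed for breaching one of them, the removal is informative for the very outcome being summarised. In a cohort of 40, a single omitted severe event can decide whether the summary shows none or one.

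The point does not depend on whether the FAS suits the progression-free survival test. The sponsor could keep the FAS as it is for efficacy and would still need an exposure-based set for safety.

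**Working it through.** **1. Set membership.** Let E be all patients included, T those who received study treatment at least once, W those who withdrew consent before treatment, and V those later found to breach a major criterion that would have barred treatment.

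- FAS = E minus W minus V (Full Analysis Population, second paragraph).
- Safety population = FAS ∩ T (Safety Population).
- Treated patients lost = T minus (FAS ∩ T) = (T ∩ W) ∪ (T ∩ V).
- T ∩ W is empty, because these patients withdrew before treatment began.
- The treated patients lost are therefore exactly T ∩ V.

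The phrase "about whom it becomes known that major in/exclusion criteria were violated" describes a breach that comes to light afterwards, and the clause does not exempt patients already treated. So T ∩ V can contain patients.

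**2. The plan's own figures.** The article gives no expected toxicity rate and no expected number of violators, so there is no planned safety figure to reproduce. Its sample size (37 evaluable, 40 recruited) rests on the progression-free survival test and is not affected.

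**3. Illustration (assumed inputs: 40 treated, 2 removed, one severe event, in one of those 2).** Exact (Clopper-Pearson) 95% intervals:

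- As written, 0/38: upper limit = 1 − 0.025^(1/38) = 0.0925, so 0% with CI 0 to 9.3%.
- All exposed, 1/40 = 2.5%: lower limit = 1 − 0.975^(1/40) = 0.0006. The upper limit solves (1 − p)^40 + 40p(1 − p)^39 = 0.025, giving p = 0.132. The CI is 0.1 to 13.2%.

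**4. Range over the number removed (assumed k = 1 to 4 of 40, each with a severe event, which is an extreme case).** The denominator is 40 − k, that is 39 down to 36.

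| Severe events among the others | Reported as written | All exposed |
|---|---|---|
| 0 | 0% | 1/40 = 2.5% to 4/40 = 10% |
| 2 | 2/39 = 5.1% to 2/36 = 5.6% | 3/40 = 7.5% to 6/40 = 15.0% |

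In the second row the gap is 7.5 − 5.1 = 2.4 points at k = 1 and 15.0 − 5.6 = 9.4 points at k = 4.

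**5. A milder case (assumed: 10% removed, at three times a 5% risk).** All exposed: 0.9 × 5% + 0.1 × 15% = 6.0%. As written: 5.0%. The understatement is 1.0 point, or 1.0/6.0 = 17% in relative terms.

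**6. No difference in risk.** If removed patients have the same risk as the rest, the expected rate is unchanged and only precision is lost. If k = 0, nothing changes.

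**The case against.** Several counter-arguments carry weight.

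- **Only major breaches count.** The clause removes patients whose breach was major and would have barred treatment, not every ineligible patient. The article does not define major. This stands, and it limits the scope.
- **The FAS text pulls both ways.** Its first paragraph keeps patients despite a violation at treatment start. The more specific second paragraph probably governs, but the two conflict and the number lost is uncertain. This shows a need for correction and does not rescue the safety definition.
- **Toxicity might be reported elsewhere.** A reader might infer that the affected patients disappear from every toxicity table, or that their events are never reported. The documents do not show that. Descriptive Analysis names no population, and Follow-up applies CTCAE reporting without limiting it to the FAS. What follows is narrower: these patients are outside the only defined safety set, and hence outside rates summarised on it.
- **Bias need not be downward.** A reader might also infer that the reported rate must be too low. Histology, Simpson grade, the 12-week interval and participation in another trial have no evident link to higher toxicity. Earlier brain radiotherapy is a weak example, because Inclusion criteria require prior photon radiotherapy of 48 to 52 Gy while Exclusion criteria bar "previous radiotherapy of the brain". Until these are reconciled, nobody can say who breaches that criterion.
- **The analysis is descriptive and the numbers are assumed.** Both are true. In the milder case the difference is one percentage point, small beside the width of an interval at n = 40.

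The argument that this could be left to the analysis plan does not hold: the article does not leave the definition open but fixes it.

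**Conclusion.** The point holds in a limited form. As written, a treated patient later found to have breached a major, treatment-barring criterion is excluded from the safety population and so from the toxicity rates summarised on it. This follows from the two definitions alone and needs no numerical assumption.

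The size of the effect is not determined by the documents. It is zero if there are no such patients. In the assumed illustration it is the difference between 0/38 and 1/40. Understatement is possible, and likely only where the breached criterion is linked to toxicity risk. A general claim of bias, or of events going unreported, goes beyond the text. The correction should nevertheless be made, because a descriptive safety summary of 40 patients is sensitive to one omitted event and the change is simple.

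**What to change.** Replace the Safety Population sentence with:

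> The safety population comprises all enrolled patients who received at least one fraction of study treatment, regardless of eligibility or FAS membership.

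Alongside it:

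- State whether study treatment in this definition means the carbon boost, the photon course or both. Treatment Schedule lists only the boost, Inclusion criteria treat the photon course as prior therapy, and Treatment Planning covers both. These must be reconciled, since they decide whether a patient who received photons only is counted.
- Name the safety population in Descriptive Analysis as the basis of the adverse event tables, and flag treated but ineligible patients in the toxicity listing.
- Reconcile the two paragraphs of Full Analysis Population, and the inclusion and exclusion criteria on earlier radiotherapy, so that it is clear who counts as a violator.

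The cost is a few sentences of wording. The sample size and the efficacy test do not change, and no extra data are needed. The reported toxicity rate may become slightly less favourable.
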